## Abstract

**Background:**

Heart failure (HF) significantly reduces functional capacity and quality of life in patients classified as New York Heart Association (NYHA) functional class II–III. While cardiopulmonary rehabilitation (CR) is beneficial, innovative strategies are required to improve accessibility and effectiveness for individuals unable to tolerate high hemodynamic loads.

**Aims:**

To compare the effects of conventional moderate-to-high intensity resistance training (CRT) versus low-load resistance training combined with blood flow restriction (BFRRT) on clinical, functional, and biochemical outcomes in HF patients.

**Methods and analysis:**

This randomized, prospective, parallel-group clinical trial will include 52 patients (NYHA II–III) allocated into CRT (60–80% 1RM) or BFRRT (20–30% 1RM, calibrated at 50% arterial occlusion pressure) groups. The supervised intervention lasts 4 months, with an 8-month post-intervention follow-up. The primary outcome is the change in serum NT-proBNP levels. Secondary outcomes include quality of life, echocardiographic ventricular function, functional capacity, and clinical events. Advanced statistical models and exploratory machine learning analyses with k-fold cross-validation will be utilized for predictive modeling and exploring personalized medicine strategies.

**Implications:**

The REHAB-WASHOUT HF trial aims to establish an effective, safe, and accessible therapeutic approach for HF rehabilitation, potentially enhancing clinical outcomes and guiding personalized prescriptive strategies in cardiovascular rehabilitation.

**Ethics and registration:**

Approved by the local institutional review board (No. 5.848.965; CAAE 64955022.9.1001.0029). Trial registration: RBR-5y8k7d7.

## Introduction

1

Heart Failure (HF) imposes a substantial burden on healthcare systems, generating costs exceeding US$100 billion annually and affecting more than 64 million people worldwide [1,2]. Although advanced pharmacological strategies—such as Angiotensin Receptor-Neprilysin Inhibitors and Sodium-Glucose Cotransporter 2 Inhibitors—have recently entered the market, the quality of life of patients with HF remains severely impaired, particularly in low-access and low-socioeconomic status contexts [3].

**Table 1 tbl1:** Schedule of enrollment, interventions, and assessments (REHAB-WASHOUT HF).

Phase	Enrollment	Baseline (T0)	Adaptation & 1RM	Intervention (16 weeks)	Post-intervention (T1)	Follow-up (T2)
**Timepoint**	Weeks −3 to −2	Weeks −2 to −1	Weeks 1–3	Weeks 4–15	Week 16 (Month 4)	Month 12
**ENROLLMENT**						
Eligibility screening	X					
Informed consent	X					
Randomization		X				
**INTERVENTIONS**						
Adaptation (CRT only)			X			
Supervised exercise (2×/wk)				X		
Unsupervised activity counseling					X	X
**ASSESSMENTS**						
Clinical (DXA, skinfolds, ABI)		X			X	X
Biochemical (BNP/NT-proBNP, microRNA)		X			X	X
Functional (CPET, 6MWT, sit-to-stand)		X			X	X
Imaging (transthoracic echocardiogram)		X			X	X
Strength (1RM test and retest)		X	X	X (adjustment)	X	X
Strength (isokinetic & handgrip)		X			X	X
Quality of life (Minnesota MLHFQ)		X			X	X
Clinical events & hospitalizations				X	X	X

**Fig. 1 fig1:**
[figure not shown]
Flow chart of study procedures.

Currently, cardiopulmonary rehabilitation (CR) holds a class I recommendation in guidelines from both the European Society of Cardiology and the American College of Cardiology [4,5]. Despite the established therapeutic role of physical training in HF populations, the heterogeneity of exercise interventions limits the consensus on the most effective prescription [6]. Furthermore, the limited global availability of structured rehabilitation programs negatively impacts patient outcomes and quality of life [7,8].

In part, the severe exercise intolerance observed in these patients reduces adherence and compromises the expected prognosis in conventional programs [9]. Traditional resistance training (CRT) typically requires moderate-to-high external loads (60–80% of 1-repetition maximum [1RM]) to induce muscular hypertrophy and strength gains. However, such intensities induce elevated central hemodynamic stress, which is often intolerable or contraindicated for individuals with advanced HF [10].

To overcome these limitations, resistance training combined with blood flow restriction (BFRRT) has emerged as a promising clinical strategy, having demonstrated safety and efficacy in other cardiovascular populations such as coronary artery disease and hypertension. By applying partial vascular occlusion to the working limbs, BFRRT allows the use of low external loads (20–30% 1RM) while mimicking the metabolic stress and hypertrophic stimuli of high-load training, thereby minimizing central cardiac overload [11,12]. However, evidence regarding BFRRT specifically in heart failure remains limited.

Therefore, this study aims to compare the effects of low-intensity resistance training versus resistance training with blood flow restriction (BFRRT) on clinical and functional outcomes in patients with HF. The primary objective is to evaluate the progression of serum N-terminal pro-brain natriuretic peptide (NT-proBNP) levels before and after a 4-month intervention. As secondary objectives, this trial will assess the impact of these protocols on health-related quality of life, functional capacity, muscular strength, left and right ventricular function, and clinical adverse events. The clinical impact will be monitored over 12 months, comprising a 4-month supervised exercise intervention with differing loading intensities followed by an 8-month period of physical activity maintenance at home with subsequent reassessment. Overall, this trial will provide novel insights into the feasibility, safety, and physiological adaptations of BFR in heart failure, establishing an accessible therapeutic paradigm for cardiovascular rehabilitation.

## Methods

2

### Study design and ethical approvals

2.1

This is a single-center, prospective, randomized, parallel-group, open-label clinical trial protocol designed to compare the effects of two cardiopulmonary rehabilitation (CR) protocols—resistance training with versus without blood flow restriction (BFRRT)—in patients with heart failure (HF).

This study protocol is structured and will be reported in accordance with the Standard Protocol Items: Recommendations for Interventional Trials (SPIRIT) guidelines. The study protocol received ethical approval from the Institutional Review Board of the Catholic University of Brasília (UCB) (Brasília, Brazil) under protocol number CAAE 64955022.9.1001.0029.

Written informed consent will be obtained from all participants prior to their formal inclusion in the trial. The investigation will be conducted in strict accordance with the ethical principles outlined in the Declaration of Helsinki (Table 1).

### Sample size calculation

2.2

The sample size calculation was informed by the data reported by Tanaka et al. [13], who evaluated a BFR-based exercise protocol in patients with HF (New York Heart Association [NYHA] functional class I or II). In their trial, a post-training reduction in brain natriuretic peptide (BNP) of 73 ± 68 pg/mL was observed in the BFR group, compared to a reduction of 15 ± 70 pg/mL in the conventional CR control group [13].

Based on these values, a Cohen's *d* effect size of 0.83 was calculated. Assuming a 1:1 allocation ratio between the experimental arms, a minimum of 24 patients per group is required to achieve a statistical power of 80% with a two-tailed alpha level of 0.05. To account for an anticipated attrition rate of approximately 10%, the final sample size has been established at 26 patients per treatment arm, resulting in a total target recruitment of 52 participants. BNP data from Tanaka et al. were used as the closest available proxy because both biomarkers reflect cardiac wall stress and no directly comparable BFR exercise trial reporting NT-proBNP was available, although this trial will evaluate N-terminal pro-brain natriuretic peptide (NT-proBNP) as its primary biochemical outcome.

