#### Inclusion criteria

2.4.1

Patients aged between 40 and 70 years; Documented diagnosis of heart failure with reduced ejection fraction (HFrEF) or heart failure with preserved ejection fraction (HFpEF); Classification within the New York Heart Association (NYHA) functional class II or III; Optimization of stable medical therapy for at least 6 weeks prior to enrollment, which must include a beta-blocker combined with either an angiotensin-converting enzyme inhibitor, an angiotensin receptor blocker, or an angiotensin receptor-neprilysin inhibitor.

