#### Randomization and allocation concealment

2.5.3

Following the completion of baseline assessments, participants will be randomly assigned (1:1) to either the Conventional Resistance Training (CRT) group or the Blood Flow Restriction Resistance Training (BFRRT) group. Randomization will be executed using an automated, computer-generated sequence with a permuted block design (block size of 2) to ensure a strictly balanced allocation between the treatment arms.

To maintain strict allocation concealment, the randomization sequence will be generated and managed by an independent research coordinator who is not involved in participant recruitment, daily interventions, or outcome evaluations. Individual group assignments will be enclosed in sequentially numbered, opaque, sealed envelopes, which will be opened only after the participant completes all baseline evaluations.

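### HF phenotype and NYHA class are neither stratified for nor named as covariates in a mixed sample of 52; the 80% power is also conditional on NYHA I–II data and has no reserve

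*Protocol article*

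**What the plan says.** **Who is enrolled.** Protocol article, section 2.4.1, requires "Classification within the New York Heart Association (NYHA) functional class II or III" and accepts a documented diagnosis of either HFrEF or HFpEF.

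**How they are allocated.** Section 2.5.3: "Randomization will be executed using an automated, computer-generated sequence with a permuted block design (block size of 2"). No stratification factor is named.

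**How they are analysed.** Section 2.5.21 specifies ANCOVA adjusted for age and sex. HF phenotype and NYHA class are not named. Section 2.5.18 adds that the biochemical markers will serve as baseline covariates, without saying in which model.

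**How the trial was sized.** Section 2.2 relies on one earlier trial, "who evaluated a BFR-based exercise protocol in patients with HF (New York Heart Association [NYHA] functional class I or II"). There, "a post-training reduction in brain natriuretic peptide (BNP) of 73 ± 68 pg/mL was observed in the BFR group", against "a reduction of 15 ± 70 pg/mL in the conventional CR control group". From these an "effect size of 0.83 was calculated" and "a minimum of 24 patients per group is required to achieve a statistical power of 80% with a two-tailed alpha level of 0.05". The target of 26 per arm allows for about 10% attrition. The section justifies using BNP in place of NT-proBNP. It does not comment on the change of NYHA range.

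**The concern.** Phenotype and NYHA class are both known before randomisation, and both could plausibly relate to NT-proBNP and its change. Phenotype is defined by ejection fraction, so it bears directly on LVEF, a secondary outcome. With only 52 patients, one unstratified sequence can leave the arms visibly different in phenotype mix, and a model with age and sex alone does not correct for it. The comparison stays unbiased over repeated randomisations, but this trial's estimate would carry noise that could have been removed cheaply, and a reader would have a ready reason to doubt it.

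The second issue is what the 80% rests on. The source trial and this one share class II only: class I is out and class III is in. Section 2.2 carries the standardised effect across that change without saying that it is an assumption.

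**Working it through.** **1. The plan's own figure.** Inputs from section 2.2: changes of 73 and 15 pg/mL, SDs 68 and 70, two-sided alpha 0.05, power 80%, 1:1 allocation.

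- Pooled SD = √((68² + 70²)/2) = 69.0; difference = 73 − 15 = 58; d = 58/69.0 = 0.84. The stated 0.83 equals 58/70.
- Two-sample t-test at d = 0.83: 23.8, so 24 per group. The stated size is reproduced.
- Power at 24 per arm: 80.4% for d = 0.83 and 81.3% for d = 0.84.

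**2. Reserve.** The smallest d with 80% power at 24 per arm is 0.826, against 0.83 planned. With 10% attrition, 26 × 0.9 = 23.4; 23 per arm gives 78.6% (d = 0.83) to 79.6% (d = 0.84).

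**3. Power over a range of d** (24 per arm; the values of d are assumptions):

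| d | Power | n per arm for 80% |
|---|---|---|
| 0.83 | 80% | 24 |
| 0.70 | 66% | 34 |
| 0.60 | 53% | 45 |
| 0.50 | 40% | 64 |

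**4. Chance imbalance in phenotype.** The documents give no expected split, so 26/26 is an assumption. Let k be the number of HFrEF patients in one arm of 26. Then P(k) = C(26,k)·C(26,26−k)/C(52,26), and the arms differ by D = 2k − 26.

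- P(k = 13) = 0.218; P(k = 12) = P(k = 14) = 0.188; P(k = 11) = P(k = 15) = 0.120.
- P(|D| ≥ 4) = 1 − 0.218 − 2 × 0.188 = 0.406.
- P(|D| ≥ 6) = 0.406 − 2 × 0.120 = 0.165 (unrounded terms).
- Simulating the actual blocks of 2 (200,000 trials) gives about 40% and 16%, so ignoring the blocks does not matter.
- The same formula with a 20/32 split gives 39% and 15%; with 16/36, 37% and 13%.

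A difference of 6 means 16/26 against 10/26, or 61.5% against 38.5%. Any outcome gap between phenotypes then enters the unadjusted arm difference multiplied by 0.23. A difference of 4 (15 against 11) gives a multiplier of 0.15.

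**5. Cost and gain of two added covariates.** With N = 48 analysed and q = 2 covariates, the expected variance inflation from estimating them is 1 + q/(N − q − 3) = 1 + 2/43 = 1.047, on 44 degrees of freedom. At d = 0.83 the noncentrality falls from 0.83 × √12 = 2.875 to 2.875/√1.047 = 2.81.

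| Outcome variance explained by the two factors | Power |
|---|---|
| Not in the model | 80.4% |
| 0% | 78.5% |
| 5% | 80.5% |
| 10% | 82.6% |
| 20% | 86.7% |

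The break-even is about 5%. Starting instead from a model that already holds age and sex (q = 2, rising to q = 4) gives the same pattern: 78.5% falls to 76.5%, and is regained at 5%.

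**The case against.** The case against has several sound parts.

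- **A reader might infer that true power is below 80%.** Holding 58 pg/mL fixed and enlarging the SD by 1.25, 1.5 or 2 times does give 63%, 48% or 30%. But those multipliers are assumptions. The documents give no SD or effect for NYHA II–III. If the difference grew in proportion to the SD, d and power would not change. With SD × 1.5 and difference × 1.25, d = 0.84 × 1.25/1.5 = 0.70 and power is 66%. What the plan carries over is d for BNP, not a pg/mL difference in NT-proBNP, and section 2.5.21 allows a log transformation. Neither the size nor the direction of any change can be derived.
- **A reader might infer that the source trial had a different ejection-fraction mix.** Its phenotype is not stated, so only the NYHA contrast is documented, and that contrast is partial because class II is common to both.
- **A reader might infer that a null result would be taken as equal effect.** No equivalence or non-inferiority claim appears.
- **Unstratified allocation is legitimate.** Randomisation-based inference already covers chance imbalance, and stratification has no bearing on whether d = 0.83 applies. Both are correct; the gain is precision and credibility, not removal of bias.
- **The plan does something about heterogeneity.** Eligibility limits age and requires stable therapy, section 2.5.18 offers biochemical markers as covariates, and later sections use echocardiography and clustering to describe phenotypes. None of this balances or adjusts for phenotype or NYHA class in the stated ANCOVA.
- **Covariates can be left to a statistical analysis plan.** True in general, but this article does fix a covariate set, so adding two factors to it is a fair suggestion.

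**Conclusion.** This is a worthwhile low-cost improvement, not an error in the plan. In a sample mixed by phenotype and NYHA class, neither factor enters the allocation or the named covariates. Under an assumed 26/26 split, a difference of 4 or more patients of one phenotype occurs in about 41% of trials, and of 6 or more in about 16%. The harm depends on phenotype being prognostic, which is plausible but is not quantified in the documents. Adjustment pays for itself once the two factors explain about 5% of the outcome variance.

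The sample-size arithmetic is right. The 80% is conditional on an effect seen in NYHA I–II patients and has no margin, and section 2.2 should say so. A shortfall in true power is possible but not shown.

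**What to change.** 1. **Section 2.5.3:** if enrolment has not begun, generate separate randomisation lists for HFrEF and HFpEF, with one written definition of the stratum. Cost: two sets of sealed envelopes instead of one. If enrolment is under way, leave the list alone and rely on item 2.
2. **Section 2.5.21:** add HF phenotype and NYHA class to age and sex in the primary model, fixed before outcome data are seen. Both are eligibility criteria, so no new data are needed. Cost: two degrees of freedom, and about 2 points of power if neither factor is prognostic.
3. **Section 2.2:** state that the 80% assumes that the standardised effect reported in NYHA I–II patients also holds in NYHA II–III patients, and show power over a range of d, for example 0.83, 0.70 and 0.60 (80%, 66%, 53%). Cost: a sentence or two and a less favourable-looking statement of power.

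No increase in sample size is asked for.

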### Participants and recruitment

2.3

Participants will be recruited from the outpatient cardiology clinics of the Catholic University of Brasília (UCB) and the State Department of Health of the Federal District (SES−DF), including primary healthcare units, the Gama Regional Hospital (HRG), and the Guará Regional Hospital (HRGu). Medical records will be screened prospectively to identify potentially eligible candidates (Figure 1).

### Eligibility criteria

2.4

Eligibility criteria will be applied through a rigorous multi-stage screening process based on the following inclusion and exclusion parameters.

#### Inclusion criteria

2.4.1

Patients aged between 40 and 70 years; Documented diagnosis of heart failure with reduced ejection fraction (HFrEF) or heart failure with preserved ejection fraction (HFpEF); Classification within the New York Heart Association (NYHA) functional class II or III; Optimization of stable medical therapy for at least 6 weeks prior to enrollment, which must include a beta-blocker combined with either an angiotensin-converting enzyme inhibitor, an angiotensin receptor blocker, or an angiotensin receptor-neprilysin inhibitor.

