#### Secondary outcomes

2.5.2

To capture a comprehensive clinical profile of the chronic adaptations induced by the training protocols, the following secondary outcomes will be evaluated at baseline and after 16 weeks:

Health-Related Quality of life: Assessed using the Minnesota Living with Heart Failure Questionnaire. This specific instrument evaluates the patients' perceptions of how the disease affects their physical, socioeconomic, and emotional dimensions, acting as a powerful clinical predictor of disease stability and patient independence.

Functional Capacity and Exercise Tolerance: Measured via the distance covered in the 6-Minute Walk Test. Functional capacity is an independent predictor of all-cause mortality in heart failure, and its improvement directly relates to real-world functional independence.

Peripheral Muscular Strength: Evaluated through the submaximal one-repetition maximum 1RM prediction protocol. Skeletal muscle wasting and weakness are core features of the pathophysiological progression of heart failure; enhancements in peripheral muscular strength are strongly linked to improved mechanical efficiency and reduced clinical frailty.

Echocardiographic Ventricular Function: Left and right ventricular structural and functional remodeling will be assessed via resting transthoracic echocardiography. Key parameters include left ventricular ejection fraction (LVEF), tricuspid annular plane systolic excursion (TAPSE), and diastolic filling pressures (*E/e'* ratio) to document central cardiac adaptations.

Clinical Safety and Adverse Events: The occurrence of any relative or absolute adverse event (e.g., symptomatic hypotension, persistent muscular pain, dizziness, or pre-syncope), all-cause hospitalizations, or clinical worsening of the heart failure condition will be systematically recorded throughout the 16-week cycle to establish safety parameters.

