#### Transthoracic echocardiogram

2.5.19

Echocardiographic images will be acquired according to the clinical recommendations of the American Society of Echocardiography using a commercially available Philips Affiniti 70 ultrasound system (Philips Ultrasound, Andover, Massachusetts, USA) equipped with a X5-1 transducer operating between 1 and 5 MHz.

The assessment of diastolic dysfunction and reduced left ventricular ejection fraction (defined as less than or equal to 54 percent for women and less than or equal to 52 percent for men) will be characterized according to current consensus guidelines [24,25]. Left ventricular end-diastolic diameter, interventricular septum thickness, and left ventricular posterior wall thickness will be measured at end-diastole. Left ventricular mass will be calculated according to the Devereux formula [24].

The left ventricular mass index will be calculated by dividing the total left ventricular mass by the body surface area, with the latter determined using the Mosteller formula [26]. Ventricular hypertrophy will be defined as a left ventricular mass index greater than or equal to 102 g per square meter for men and greater than or equal to 88 g per square meter for women [24]. Three consecutive cardiac cycles of all images obtained in the apical axes (four-chamber, two-chamber, and three-chamber views) will be acquired, alongside targeted recordings from the apical four-chamber windows focused specifically on the right ventricle [27]. These recordings will serve to perform advanced deformation analysis of the left ventricular global longitudinal strain, right ventricular free wall strain, and left atrial strain.

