To optimize the echocardiographic assessment via speckle tracking, images will be captured at a high temporal resolution of 40–70 frames per second [28]. Subsequently, these digital cardiac cycles will be transferred to a dedicated QLAB workstation (version 10.2, Philips, the Netherlands) for multi-chamber strain analysis. Peak longitudinal regional strain will be measured across the 17 myocardial segments of the left ventricle, and a weighted average will be computed to determine the final left ventricular global longitudinal strain value [25]. Left ventricular global longitudinal strain values higher than minus 16 percent (meaning lower than 16 percent in absolute value) will be classified as abnormal [28]. Right ventricular longitudinal strain will be analyzed utilizing the right ventricle-focused apical four-chamber view, and the average strain value will be obtained from the three anatomical segments of the right ventricular free wall [29]. A free wall right ventricular longitudinal strain value higher than minus 20 percent (lower than 20 percent in absolute value) will be considered abnormal, complying with the 2015 European Association of Cardiovascular Imaging and American Society of Echocardiography chamber quantification guidelines and the recent multinational World Advisory Strain Evaluation study [25,26,30].

Left atrial strain analysis will be executed using the dedicated left atrial automated function imaging software package and will be based on both the left atrium-focused four-chamber and two-chamber views [31]. The total left atrial reservoir strain, which possesses the largest body of clinical evidence supporting its prognostic utility in heart failure, will be reported [32]. The lower normal limit for the left atrial reservoir strain will be set at 16.7 percent [31]. Importantly, these multi-chamber echocardiographic metrics will be utilized to robustly characterize the phenotypic heart failure profiles of the sample and to strictly exclude patients presenting with severe uncorrected valvular diseases or obstructive hypertrophic cardiomyopathy, ensuring absolute hemodynamic safety prior to the exercise protocols.

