#### Statistical analysis and machine learning plan

2.5.21

All primary and secondary clinical, functional, and biochemical outcome analyses will be conducted strictly based on the intention-to-treat principle. Accordingly, all randomized participants will be evaluated within their originally allocated treatment groups, regardless of compliance, session attendance, missing data, or subsequent protocol deviations. Continuous variables will be presented as mean plus or minus standard deviation for data with a normal distribution, or as median and interquartile range for non-normally distributed data.

Categorical variables will be expressed as absolute frequencies and percentages and will be compared utilizing the chi-square test. Continuous variables demonstrating normal distribution will be analyzed using analysis of covariance models, adjusted for age and sex as clinical baseline covariates. The essential prerequisites for the analysis of covariance models—including linearity, normality of distribution, and homogeneity of variance—will be strictly verified through visual inspection of histograms, normal probability plots, and residual scatter plots.

Continuous variables with non-normal distribution will undergo logarithmic transformation to correct distribution asymmetry. If normal distribution is not achieved following transformation, generalized linear models or robust statistical methods will be applied to guarantee appropriate adjustments for age and sex. All classical statistical analyses will be conducted utilizing the R Studio environment (version 1.12, R language version 4.2).

In addition to traditional frequentist statistical analyses, advanced machine learning and artificial intelligence techniques will be deployed to optimize data interpretation and discover predictive biomarkers of therapeutic response to the physical exercise interventions. To predict individual clinical responses to the cardiovascular rehabilitation protocol—specifically changes in N-terminal pro-brain natriuretic peptide, peak oxygen consumption, and quality of life scores—supervised learning algorithms will be implemented, including random forest, gradient boosting machines, and support vector machines. To mitigate the risk of model overfitting and ensure generalizability, these supervised algorithms will be evaluated using a k-fold cross-validation strategy.

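### HFrEF and HFpEF patients are randomised in one sequence with no stated stratification, and the ANCOVA adjusts only for age and sex, so chance imbalance in phenotype is left in the NT-proBNP and echo comparisons

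*Protocol article*

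**What the plan says.** Four statements in the protocol article bear on this point.

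- **Population (2.4.1).** Entry requires "Documented diagnosis of heart failure with reduced ejection fraction (HFrEF) or heart failure with preserved ejection fraction (HFpEF"). The criterion is the documented diagnosis; the article gives no ejection-fraction limit for either label.
- **Allocation (2.5.3).** Participants are assigned 1:1 from a computer-generated sequence with a "permuted block design (block size of 2"). No stratification factor is named. Blocks of two keep the arm sizes equal but do nothing for phenotype.
- **Outcomes (2.5.1 and 2.5.2).** The primary outcome is NT-proBNP change over 16 weeks. For ventricular function, "Key parameters include left ventricular ejection fraction (LVEF), tricuspid annular plane systolic excursion (TAPSE), and diastolic filling pressures" (the E/e' ratio) are measured in all patients, the purpose being, for the set as a whole, "ratio) to document central cardiac adaptations".
- **Analysis (2.5.21).** Normally distributed outcomes go to ANCOVA models "adjusted for age and sex as clinical baseline covariates". The fallback for outcomes still non-normal after log transformation, generalized linear or robust methods, also names age and sex alone.

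Section 2.5.19 also gives the article's only ejection-fraction cut-off, for "reduced left ventricular ejection fraction (defined as less than or equal to 54 percent for women and less than or equal to 52 percent" (the second figure applies to men), and later says that the echo metrics will be "utilized to robustly characterize the phenotypic heart failure profiles of the sample".

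**The concern.** HFrEF and HFpEF are defined by ejection fraction, and ejection fraction is itself one of the outcomes. Phenotype is thus a plausible prognostic factor for the echo outcomes, and probably for NT-proBNP. A baseline factor of that kind is normally handled in the randomisation, in the model, or in both. Here the stated rules do neither.

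With 52 patients, one chance split of phenotype can be large enough to colour a secondary comparison. If the average change differs between phenotypes, part of the observed difference between arms would come from the mix and not from the training method. Across possible randomisations this averages to zero, but the trial is run once, and the spread that phenotype adds to the outcome stays in the error term.

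**Working it through.** **The plan's own figure.** Section 2.2 bases the sample size on BNP reductions of 73 ± 68 and 15 ± 70 pg/mL.

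- Pooled SD = √((68² + 70²)/2) = 69.0, so d = 58/69.0 = 0.84. The article states 0.83 (58/70 = 0.829).
- A two-sample t-test at d = 0.83, two-sided alpha 0.05 and 80% power needs 23.8, so 24 per arm, as stated (power at 24 is 80.4%).
- 24/0.9 = 26.7, against the stated 26 per arm.

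The figure reproduces closely. It concerns a natriuretic peptide and takes no account of phenotype, so it neither supports nor refutes this point.

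**How large can the imbalance be?** Inputs from the article: 26 per arm, 52 in total, no stratification. Assumed, because not given: an HFpEF share of 25%, 50% or 75%. If phenotype is unrelated to the order of enrolment, the number of HFpEF patients in one arm is hypergeometric (52 patients, K with HFpEF, 26 drawn), and the imbalance is |2k − K|/26.

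| Assumed HFpEF share | K | SD of imbalance | P(imbalance ≥ 20 points) |
|---|---|---|---|
| 25% | 13 | 12 points | 5% |
| 50% | 26 | 14 points | 16% |
| 75% | 39 | 12 points | 5% |

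The SD at 50% is (2/26) × √(26 × 0.5 × 0.5 × 26/51) = 0.14. Counts are whole numbers, so the smallest imbalance counted is 6/26 = 23 points at a 50% share and 7/26 = 27 points at 25% or 75%. With 48 evaluable patients the probabilities are 15% at a 50% share and 9% at 25% or 75%.

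**What does it do to the comparison?** Let δ be the difference in mean change between phenotypes, in units of the within-phenotype SD. The article gives no value, so a range is assumed. At a 50% share:

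- shift in the arm difference = imbalance × δ
- unadjusted standard error = √((2/26) × (1 + 0.25δ²))
- standard error with phenotype variation removed = √(2/26) = 0.277

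| Assumed δ | Shift at 6/26 imbalance | Unadjusted SE | Ratio to 0.277 |
|---|---|---|---|
| 0.25 | 0.06 | 0.280 | 1.01 |
| 0.50 | 0.12 | 0.286 | 1.03 |
| 1.00 | 0.23 | 0.310 | 1.12 |

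**What does the covariate cost?** The expected squared correlation between arm and phenotype under this allocation is 1/51, about 2%, so adjustment inflates the variance by about 2% on average. It pays for itself once 0.25δ² exceeds 0.02, that is, once δ is above about 0.28.

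**The case against.** The case against making much of this is fair, and most of it stands.

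- **A broad population is a legitimate choice.** Enrolling both phenotypes is not an error. This stands.
- **Concealed randomisation protects against bias.** Chance imbalance is part of the sampling variation that the confidence interval reflects. The primary outcome is a change from baseline, so a different starting level does not pass directly into it; phenotype matters only if the change itself differs. This stands, and it is why the point is about precision.
- **An unstratified design with two covariates is a common choice.** True, but the article fixes the covariate set and leaves out the factor by which its own population is defined.

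Three stronger readings are tempting, and the document does not support them.

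1. *The left-ventricular effect is diluted by pooling.* Suppose d = 0.83 in HFrEF and zero in HFpEF, with a common SD and 24 per arm. Then HFpEF shares of 25%, 50% and 75% give d = 0.62, 0.42 and 0.21, with power of 56%, 29% and 11%. But 0.83 comes from BNP, not LVEF; the zero effect and the shares are assumed; and an equal effect in both phenotypes means no dilution. The ventricular objective also rests on TAPSE and E/e', not on LVEF alone.
2. *Phenotypes will be misclassified.* Section 2.5.19 defines reduced LVEF as "defined as less than or equal to 54 percent for women and less than or equal to 52 percent for men", but nothing in the article uses that limit to decide entry, assign a phenotype or form an analysis group.
3. *The limit does not fit the entry groups.* Showing this would need ejection-fraction limits for the two labels. The article gives none, and an article may leave them to the full protocol.

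**Conclusion.** The point holds as a modest one about the stated adjustment set. Both phenotypes are enrolled, no stratification is stated, and the models name age and sex only, so chance phenotype imbalance is left unadjusted in the NT-proBNP and echo comparisons.

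The chance of an imbalance of 20 points or more is about 5% to 16% over assumed HFpEF shares of 25% to 75%. At a 50% share, a 23-point imbalance shifts the arm difference by 0.06 to 0.23 SD when the phenotypes differ in mean change by 0.25 to 1.0 SD. Even at the top of that range the shift is smaller than one standard error (0.31). So it could colour the reading of a secondary result, but would rarely decide it. The size rests on the assumed share, on the assumed phenotype difference, and on phenotype being unrelated to enrolment order.

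A reader might infer biased treatment comparisons, an undersized trial or misclassified patients. None of these follows: there is no systematic bias, the primary sample size is not shown to be wrong by this argument, and misclassification would need a use of the echo limit that the article does not describe.

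**What to change.** 1. In 2.5.21, add entry phenotype (HFrEF or HFpEF, as documented at enrolment) to age and sex in the models for NT-proBNP and the echo outcomes. Carry it into the generalized linear or robust fallback as well.
2. Report LVEF change by arm within each phenotype as a description, without subgroup tests, so that a reader can see whether the pooled mean hides different patterns.
3. In 2.5.19, say whether the 54%/52% limit for reduced LVEF is a descriptive echo reading only. If it is to play any part in phenotyping, reconcile it with the labels in 2.4.1.

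The cost is one degree of freedom, about 2% in variance when phenotype turns out to be unrelated to the outcome, and a few lines of text. No new measurement is needed. The change should be fixed before outcome data are compared by arm.
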